***Objective 3.*** Similar to IPD case-control study, we will conduct two separate case-control analyses for radiographically- confirmed pneumonia, one using hospital controls and one using community controls. To adjust for multiple confounding variables as well as to evaluate effect modification, the conditional logistic regression method designed for matched studies will be used in this analysis as well
^30^. Similar to the IPD analysis, we will also generate the adjusted OR and its 95% CI and since residual confounding by age may be an issue with this analysis as well, we will likely age adjust vaccine efficacy estimates by including a linear term for age in month in all models, as described for Objective 2. We will define VE as done in Objective 2, but in this analysis OR will indicate the odds ratio of radiologically confirmed pneumonia to PCV vaccination status
^31^. In the absence of any selection bias, the OR will estimate the incidence rate ratio.

The incidence rate of chest radiograph-confirmed pneumonia will be computed by dividing the number of radiograph-confirmed pneumonia cases by child years of observation. The 95% CI will be calculated using the Poisson distribution. Separate point and interval estimations for different types of endpoints as defined by the classifications of chest radiograph results will be computed.

To estimate the impact of the vaccine, the incidence rate ratio will be calculated by dividing the incidence rate in study months 13–24 by the incidence rate in study months 1–12; standard errors and 95% CIs will be reported. Poisson regression will be used to assess trends in the incidence rate over time. We will also investigate whether any clustering by study hospital or evaluating pediatrician is evident.

***Objective 4:*** Our analytic methodology for Objective 4 will be similar to that for Objectives 2 and 3, except that the endpoint will be ultrasound-confirmed pneumonia rather than radiographically- confirmed pneumonia.

***Objective 5:*** The primary study outcome will be prevalence of vaccine-type pneumococci (serotypes 1, 4, 5, 6B, 7F, 9V, 14, 18C, 19F, and 23F) among children with radiographically-confirmed pneumonia, stratified by vaccination status. We will calculate this prevalence rate for all children with X-ray confirmed pneumonia during a rolling calendar period, beginning the first week of NP swab collection. Standard deviations and 95% confidence intervals for the prevalence rates will be calculated. Rates will be calculated both unadjusted and adjusted for participant demographic characteristics. Rates will be plotted against time separately for vaccinated and unvaccinated participants using the midpoint of the interval as the time point shown on the x-axis, and with population prevalence of immunization superimposed, as in Loughlin
*et al.* (2014)
^32^.

In a secondary analysis, we will use a multivariate logistic regression model to test the effect of time trend, vaccination status and the interaction of time and vaccination status on carriage of VT pneumococci in this population of pediatric Bangladeshi pneumonia patients. Other analyses may explore the joint effect of vaccination status and time on carriage of NVT pneumococci.

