Risk factors for IPD: age, family structure, antibiotic use, season/date, comorbid illness status of the individual, crowding measures, smoke exposure variables, geographic location, nutritional status, birth weight, gestational age at birth, and socio-economic status;Vaccination status: Immunization status of each child including PCV, oral polio vaccine, and pentavalent vaccine is recorded. The mother is asked to provide the child’s immunization card for examination and it is extracted onto a standard data collection form. We also take a digital photograph of the immunization card. If the immunization card is not available, the caregiver is asked if the child has been vaccinated, and if so, at which immunization center. The register of the identified immunization clinic is then reviewed and the child’s immunization history is abstracted. Only children who received at least two doses of the vaccine at least fourteen days before the date of case identification or control selection will be considered as vaccinated for the purposes of the study analysis;Anthropometric measurements: Current weight, height and mid-upper arm circumference are also collected.

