### Coverage survey and incidence trend analysis

 We have conducted two PCV coverage surveys, one in August-September 2016 and the other in August-September 2017. The surveys included simple random samples of 3,753 and 5,421 vaccine age eligible children stratified by age in months and union (with an average population of 25,000; there are 30 unions in the study area), respectively. This assures that every union’s coverage of <24 month-old children can be estimated to within ten percentage points (or less) with 95% confidence during any study month. The estimated vaccine coverage for the entire area for any given month will be more precise. These data will allow us to relate vaccine coverage to disease incidence via a Poisson regression model with one observation for each union-month.

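### The Poisson trend and union-month models name no season term, overdispersion allowance or within-union correlation, so they can understate error and, over 24 months, can show a trend that is not there.

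*Protocol article*

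**What the plan says.** In the analysis plan, the Objective 3 text takes cases over child-years as the radiographic pneumonia rate and adds: "The 95% CI will be calculated using the Poisson distribution". A separate paragraph defines impact as a rate ratio obtained by "dividing the incidence rate in study months 13–24 by the incidence rate in study months 1–12", for which "standard errors and 95% CIs will be reported"; no method is given for that interval. The same paragraph continues: "Poisson regression will be used to assess trends in the incidence rate over time". Then comes the one statement about dependence: "We will also investigate whether any clustering by study hospital or evaluating pediatrician is evident". It does not say what happens to the standard errors if clustering is found. Objective 4 (ultrasound pneumonia) follows the methods of Objectives 2 and 3.

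The section on the coverage survey and incidence trend adds a model relating coverage to incidence "via a Poisson regression model with one observation for each union-month", and notes that "there are 30 unions in the study area". Each union therefore contributes repeated monthly records. Season appears only among the risk factors recorded for cases and controls ("antibiotic use, season/date, comorbid illness status of the individual"), not in the incidence analyses.

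**The concern.** A plain Poisson model takes the variance of the counts to equal their mean. Monthly pneumonia counts can vary more than that through epidemics, local clustering, repeat episodes and shifts in referral. The article itself describes conditions that could produce such variation. Village workers are paid for successful referrals, mobile teams sit with high-volume providers, and the ultrasound case volume grew enough seven months in to force a shorter form. Repeated counts from one union may also be correlated.

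A straight-line time term is also correlated with an annual cycle, even over two complete years, so an unmodelled season can appear as a rise or fall.

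The time analysis carries weight: the Discussion offers a complementary time series as the counterbalance should the radiographic case-control study prove underpowered. Intervals that are too short, or a seasonal artefact in the slope, would weaken that support in either direction.

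**Working it through.** **Inputs.** The article gives no event count, precision or power for the incidence analyses. The only case count available is the 1,130 in Table 9, planned for the case-control study and used here for scale. Table 9 is not in dispute: a matched case-control power formula with an assumed case-control exposure correlation of 0.2 returns its four detectable odds ratios (0.766, 0.800, 0.813, 0.820). Table 8 starts in August 2015 and runs 29 months. The variance-to-mean ratio φ and the seasonal amplitude are assumptions; the article gives neither.

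**Step 1: coverage under overdispersion.** Actual coverage of a nominal 95% Poisson interval = 2Φ(1.96/√φ) − 1.

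| φ (assumed) | 1.96/√φ | Coverage | Type I error |
|---|---|---|---|
| 1 | 1.96 | 95% | 5% |
| 1.5 | 1.60 | 89% | 11% |
| 2 | 1.39 | 83% | 17% |
| 3 | 1.13 | 74% | 26% |

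**Step 2: the two-year rate ratio.** With 565 cases per year, SE(log ratio) = √(φ × 2/565), and the 95% limits are the ratio divided and multiplied by exp(1.96 × SE).

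- φ = 1: SE 0.059, factor 1.124
- φ = 2: SE 0.084, factor 1.179
- φ = 3: SE 0.103, factor 1.224

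The φ = 1 line applies only if plain Poisson variance is used for the ratio, which the article does not say.

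**Step 3: seasonal artefact in the trend.** Expected monthly counts were set proportional to exp{A cos[2π(m − peak)/12]}, with A = ln(R)/2 and R the peak-to-trough ratio. They were scaled to 1,130 cases from August with no true change, and a log-linear Poisson trend without season terms was fitted for each of the 12 peak months.

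| Window | R (assumed) | Annual rate ratio across peak months | Chance of a false significant trend |
|---|---|---|---|
| 24 months | 1.5 | 0.909 to 1.100 | 7.5% to 46% |
| 24 months | 2 | 0.849 to 1.177 | 12% to 89% |
| 24 months | 3 | 0.774 to 1.293 | 20% to 99.9% |
| 29 months | 2 | 0.983 to 1.018 | at most 7% |
| 29 months | 3 | 0.969 to 1.032 | at most 11% |

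The ratio of months 13–24 to months 1–12 is exactly 1.000 for every peak month and amplitude, because each block holds one full cycle.

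**Step 4: does the remedy work?** Simulation with 1,000 runs per setting (24 or 29 months, R = 1 or 2, φ = 1 or 2, four peak months) gave these false-positive rates at nominal 5%:

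- Trend without season terms, 24 months, R = 2, φ = 1: 11.5% (January peak), 85% (April), 16.8% (July), 87.9% (October).
- Trend with 12-month sine and cosine terms but plain Poisson SE, φ = 2: 14% to 18%.
- Two-year ratio with plain Poisson SE, φ = 2: 14% to 17%.
- Trend with sine and cosine terms and Pearson-scaled (quasi-Poisson) SE: 4.1% to 6.6% in every setting.

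Season terms alone are not enough; the variance must change too. The simulated season was a single cosine, which the harmonic terms fit exactly, and union-level clustering was not simulated.

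**The case against.** The strongest reply is that a condensed article names a model family and leaves covariates and variance estimation to a fuller plan. Poisson regression is compatible with harmonic terms and robust or scaled errors, and nothing rules them out. That stands as a limit on the point: no season term is named, but none is excluded. It does not remove the point, because the model family is fixed and the one safeguard mentioned, the clustering check, has no stated consequence and does not look at unions.

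Four stronger readings are tempting and not supported:

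- A reader might apply the Poisson interval sentence to the rate ratio. It follows the definition of the single rate; the ratio has its own sentence with no method. A Poisson interval for one descriptive rate is conventional.
- A reader might infer that season biases the impact estimate. It does not if the cycle is stable, since two whole years are compared.
- A reader might infer that clustering is ignored. It is to be investigated.
- A reader might take counts here to be strongly seasonal and overdispersed as fact. The article gives no monthly counts, amplitude or dispersion figure.

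It is also fair that no window is fixed for the trend regression. Over the full span of Table 8 the seasonal artefact nearly disappears.

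**Conclusion.** The point holds in a limited form. If counts are overdispersed or correlated within union, the Poisson trend and union-month models as named understate the error: nominal 95% intervals cover about 83% at φ = 2 and 74% at φ = 3. If incidence is seasonal at 2:1, a 24-month trend without season terms can be wrong by about -15% to +18% per year, depending on the peak month. Over 29 months the error is under 2% per year. The two-year rate ratio is exposed only through its standard error, and only if plain Poisson variance is used. All these sizes rest on assumed dispersion and amplitude, and the rate-ratio standard errors and false-trend probabilities also rest on 1,130 cases borrowed from Table 9. For scale, the Discussion cites trial efficacies of 20% and 37% against radiographic pneumonia, so a spurious 15% annual fall could be mistaken for vaccine impact.

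**What to change.** For the trend and union-month models, state in advance:

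- log child-time as the offset;
- calendar-month or 12-month harmonic terms for season;
- quasi-Poisson or negative-binomial variance, with standard errors clustered on union. Thirty unions make this workable; three hospitals are too few for robust errors at that level.

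Use the same variance for the interval of the months 13–24 over months 1–12 ratio, and apply all of this to the clinical, radiographic and ultrasound pneumonia endpoints. The Poisson interval for a single descriptive rate may stay.

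This needs analysis wording only and uses data already collected. The price is wider intervals: in the example above, the rate-ratio factor goes from 1.124 to 1.179 at φ = 2.

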### Aims and objectives

The primary aim of this study is to conduct a comprehensive evaluation of the national introduction of the PCV10 in Bangladesh measuring multiple outcomes. To accomplish this aim, we have established the following objectives for the study:

**Objective 1:** To collect data on community-based pre-PCV incidence rates of IPD in children 0–59 months of age in Sylhet district of Bangladesh.

**Objective 2:** To evaluate the effectiveness of PCV10 introduction on Vaccine Type (VT) IPD in children 3–59 months of age using an incident case-control study design. Secondary aims include measuring the effects of PCV10 introduction on all IPD, regardless of serotype, in children 3–59 months of age using the case-control study design, and quantifying the emergence of Non Vaccine Type (NVT) IPD.

**Objective 3:** To evaluate the effectiveness of PCV10 introduction on chest radiograph-confirmed pneumonia in children 3–35 months of age using an incident case-control study design. An additional aim is to estimate the incidence trend of clinical and radiologically-confirmed pneumonia in 3–35 month-old children in the study area before and after introduction of the PCV10
** vaccine.

**Objective 4:** To determine the feasibility and utility of lung ultrasound for the diagnosis of pediatric pneumonia in a large sample of children in a resource-limited setting. We also sought to evaluate the effectiveness of PCV10 introduction on ultrasound-confirmed pneumonia in children 3–35 months of age using an incident case-control study design and to examine the incidence trend of ultrasound-confirmed pneumonia in 3–35 month-old children in the study area before and after introduction of the PCV10 vaccine.

**Objective 5:** To determine the direct and indirect effects of vaccination status on NP colonization on VT pneumococci among children with pneumonia.

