### Objective 5: Assessment on the impact on NP carriage

An assessment of the baseline rates of NP pneumococcal colonization among participants with radiograph-confirmed pneumonia began following the start of the chest radiograph study in September 2015. Physicians collect nasopharyngeal swabs on all consenting clinical pneumonia cases. Participants are requested to sign a separate consent for NP swab collection. NP specimens are collected using nylon flocked swabs in accordance with updated WHO core methods
^28^,^29^. A single NP specimen is collected from the posterior nasopharynx of each subject by inserting the swab, rotating it 180 degrees and removing it. The swab is inserted immediately into one mL of liquid STGG transport medium and transported on ice to the clinical laboratory in Sylhet. Swabs are frozen at -20°C and stored for up to seven days. All swabs of confirmed radiographic pneumonia cases are cultured for pneumococcus; the remaining swabs are discarded. In the lab, the specimen are vortexed, aliquoted into two separate specimens (one with the swab retained), and a sample inoculated into broth for enrichment. Following broth enrichment, the sample is plated onto a gentamicin-blood agar plate and incubated in a CO2 incubator for isolation of pneumococcus. An aliquot of the broth enrichment as well as the remaining STGG NP sample are frozen (−80°C). Pneumococci are detected based on morphology, optochin susceptibility and bile solubility.

To determine the density of pneumococcal colonization, a second sample from the STGG vial is subjected to 10-fold dilutions up to 10
. An amount of 100 μl of each dilution is plated onto gentamicin blood agar plates and the semiquantitative results are documented, based on the numbers on the plates with countable number of pneumococcal and dilution factors. Pneumococcal strains are serotyped by the capsular swelling procedure (quellung reaction) with type-specific anti-pneumococcal omni, pool, type or group, and factor sera (Statens Seruminstitute, Copenhagen, Denmark).

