We have measured NP carriage because a precursor to disease is carriage of the bacteria in the nasopharynx. If the vaccine reduces VT NP carriage, then we would potentially expect the transmission of disease to be lower and that there will be less disease. However, while up to 70% of children may be colonized with the pneumococcus in the nasopharynx, a very small proportion of these children will become ill with this disease
^43^. Nevertheless, the reduction of NP carriage is one measure of the impact of the vaccine. Moreover, reduction of NP carriage also reduces the circulation of the organism in the community and thus confers protection to unimmunized children who live in the same community – “herd immunity”
^38^.

Although chest radiographs and lung ultrasound imaging outcomes are non-specific to pneumococcus, radiographically- and sonographically-confirmed pneumonia could be markers for bacterial pneumonia. Two placebo randomized controlled trials (RCTs) in The Gambia and South Africa evaluated VE of PCV against WHO-defined radiographic pneumonia in children
^44^,^45^. These studies validated the use of the WHO-defined radiographic pneumonia definition in PCV impact studies by observing a VE of 20% (95% confidence interval (CI), 2%, 35%) in South African children without HIV-infection, and a VE of 37% (95% CI, 25%, 48%) among Gambian children against this endpoint. These RCT findings support our decision to include the WHO-defined radiographic pneumonia endpoint (i.e., primary endpoint pneumonia) in this study.

Given PCV VE is now well established against radiographic pneumonia in settings outside of South Asia, a placebo RCT designed study is no longer ethical. We are therefore utilizing both case-control and time-series designs in this PCV impact study to assess VE against radiographic pneumonia. One recent case-control study from The Gambia reported mixed results using WHO-defined radiographic pneumonia among children 3–59 months old

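### Objective 5 compares vaccine-type carriage by vaccination status only among radiographic pneumonia cases, so the contrast is not a direct effect on colonization and leans toward benefit

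*Protocol article*

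**What the plan says.** The aim is causal and concerns colonization: "To determine the direct and indirect effects of vaccination status on NP colonization on VT pneumococci among children with pneumonia" (Aims and objectives, Objective 5).

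The sampling is narrower. Under the Objective 5 methods, "Physicians collect nasopharyngeal swabs on all consenting clinical pneumonia cases", and then "All swabs of confirmed radiographic pneumonia cases are cultured for pneumococcus; the remaining swabs are discarded". No swabbing of children without pneumonia is described.

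The analysis plan for Objective 5 sets the primary outcome as VT prevalence "among children with radiographically-confirmed pneumonia, stratified by vaccination status". It adds that "Rates will be calculated both unadjusted and adjusted for participant demographic characteristics". The secondary analysis is a logistic model for time, vaccination status and "the interaction of time and vaccination status on carriage of VT pneumococci in this population of pediatric Bangladeshi pneumonia patients".

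The Discussion states that carriage is a precursor of disease. It cites two randomised trials with vaccine effectiveness (VE) against radiographic pneumonia of 20% (95% CI 2% to 35%) and 37% (95% CI 25% to 48%). On carriage it concludes: "Nevertheless, the reduction of NP carriage is one measure of the impact of the vaccine".

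**The concern.** Every child in the comparison has radiographic pneumonia. That condition lies downstream of VT carriage and is also what the vaccine is meant to prevent. Suppose vaccination stops some VT carriers from developing pneumonia. Those children never enter the vaccinated case group, while their unvaccinated counterparts enter the unvaccinated group. VT carriage then looks lower in vaccinated cases without any change in who carries the organism.

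The contrast therefore mixes two effects: one on acquiring or keeping VT carriage, and one on progression from carriage to pneumonia. Only the first is an effect on colonization, and only the first bears on transmission and herd protection. Adjustment for demographic characteristics does not separate them, because the selection works through VT disease itself. The vaccination coefficient in the secondary logistic model inherits the problem, since it is fitted to the same patients.

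At stake is whether Objective 5 can report a direct effect on colonization at all.

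**Working it through.** The article gives no sample size, effect size or power for Objective 5, so there is no figure of its own to reproduce. The check asks what the planned contrast shows when the vaccine has no effect on carriage.

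**General relation.** Among cases,

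OR(VT carriage, vaccinated vs unvaccinated) = OR in the population × (1 − VE in VT carriers) / (1 − VE in non-carriers).

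The second factor is below 1 whenever the vaccine protects VT carriers against pneumonia more than it protects non-carriers.

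**Check 1: attributable-fraction model.** All three inputs are assumed; none is in the document.
- AF, share of radiographic pneumonia caused by VT pneumococcus in unvaccinated children: 0.1 to 0.3
- bg, VT carriage in pneumonia of other cause: 0.15 to 0.25
- VE against VT pneumonia: 0.5 to 0.7

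Unvaccinated prevalence = AF + (1 − AF) × bg.
Vaccinated prevalence = [AF(1 − VE) + (1 − AF) × bg] / (1 − AF × VE).

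| AF | bg | VE | Unvaccinated | Vaccinated | Ratio |
|---|---|---|---|---|---|
| 0.1 | 0.25 | 0.5 | 0.100 + 0.225 = 0.325 | 0.275 / 0.95 = 0.289 | 0.89 |
| 0.2 | 0.25 | 0.7 | 0.200 + 0.200 = 0.400 | 0.260 / 0.86 = 0.302 | 0.76 |
| 0.3 | 0.15 | 0.7 | 0.300 + 0.105 = 0.405 | 0.195 / 0.79 = 0.247 | 0.61 |

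The implied overall VE against radiographic pneumonia is AF × VE, from 0.1 × 0.5 = 5% to 0.3 × 0.7 = 21%. The upper end is about the lower of the two trial estimates in the Discussion, so the inputs are not extreme.

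**Check 2: starting from the cited trial estimates.** Let p be VT carriage in unvaccinated cases (assumed 30% to 60%; the Discussion gives only up to 70% for any pneumococcus). Let VE be the overall effect on radiographic pneumonia, acting wholly through VT carriers. Then vaccinated prevalence = (p − VE)/(1 − VE), and OR among cases = 1 − VE/p.

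| VE | p | Vaccinated cases | OR |
|---|---|---|---|
| 20% | 30% | 12.5% | 0.33 |
| 20% | 40% | 25.0% | 0.50 |
| 20% | 50% | 37.5% | 0.60 |
| 20% | 60% | 50.0% | 0.67 |
| 37% | 40% | 4.8% | 0.075 |
| 37% | 50% | 20.6% | 0.26 |
| 37% | 60% | 36.5% | 0.38 |
| 2% (lower limit of the 20% estimate) | 50% | 49.0% | 0.96 |

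VE 37% with p = 30% is impossible in this model, because VE cannot exceed p.

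**Chance of a false finding.** Table 9's 1130 cases and 46% coverage were set for the case-control studies and are borrowed here for illustration. With a two-sided 0.05 test, the probability of a significant spurious difference is 91% at VE 20%, p = 60%, and higher in the other VE 20% and 37% rows. With 200 cases the VE 20%, p = 60% setting gives 29%.

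**Simulation check.** In 4 million simulated children, VT carriage was 30% in both groups and carriers had three times the pneumonia risk. The population OR stayed at about 1.0. Among cases it was 0.70, 0.50 and 0.19 when VE in VT carriers was 30%, 50% and 80%.

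**The case against.** The strongest reply is that the restriction is openly declared. The objective says it applies to children with pneumonia, the primary outcome is defined in radiographic cases, and the secondary model names the same patients. As a descriptive prevalence the outcome is well defined. That stands, and the outcome need not change. It does not rescue the aim, which still speaks of effects on colonization.

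A reader might infer that the Discussion already treats the result as reduced carriage and transmission. It does not. The text is a conditional rationale written without results. What can be said is that it carries no selection caveat.

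A reader might also infer that the indirect effect fails for the same reason. It does not follow: with no carriage effect, this mechanism leaves VT prevalence in unvaccinated cases flat over time. Nor does the document support a claim that a changing age mix biases that trend by some amount. It gives neither the age distribution of unvaccinated cases nor an age gradient in VT carriage. The planned adjustment of rates for demographic characteristics may well include age, and a condensed article need not list every covariate of the logistic model. Age is therefore only a secondary improvement here.

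Finally, every magnitude above is assumed or borrowed from other settings. That stands too, and it limits the claim to direction plus an illustrative range.

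**Conclusion.** The concern holds for the vaccinated-versus-unvaccinated contrast. As sampled, Objective 5 cannot identify a direct effect of vaccination on VT colonization. If the vaccine prevents pneumonia in VT carriers, the contrast is biased toward benefit, and the planned demographic adjustment cannot correct it. The direction depends on that condition alone: protection that worked only by preventing carriage would leave the odds ratio undistorted by this route.

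The size is not fixed by the document. With no true carriage effect, the illustrative prevalence ratio is 0.61 to 0.89 under the assumptions of check 1. Under check 2 the distortion ranges from negligible (OR 0.96 at VE 2%) to large. This is an error in what may be concluded from one of five objectives. It is not a fault in the outcome definition, and it does not reach the time trend in unvaccinated cases.

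**What to change.** 1. Restate the Objective 5 estimand as VT prevalence among radiographic pneumonia cases by vaccination status, and remove the claim that this contrast is a direct effect on colonization.
2. Add to the Discussion that lower VT prevalence in vaccinated cases cannot by itself be read as reduced community carriage or transmission, because it may reflect protection of carriers against pneumonia.
3. As a secondary improvement, name age in months in the time-by-vaccination logistic model. A linear age term is planned for Objective 2 and described as likely for Objective 3. Vaccine eligibility by age changes with calendar time: in Table 8 the maximum eligible age rises from 15 completed months in August 2015 to 35 in April 2017.

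The cost is wording plus one covariate already collected; the price is a weaker carriage claim. Study status reports fieldwork for this objective as complete, and swabs from cases without radiographic confirmation were discarded. Interpretation and analysis are therefore what can still be changed.
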